## Abstract

**Background:**

There have been dramatic changes in the approach to screening for aneuploidy over the last 20 years. However, the approach to screening for other complications of pregnancy such as intra-uterine growth restriction, pre-eclampsia and stillbirth remains largely unchanged. Randomised controlled trials of routine application of high tech screening methods to the general population have generally failed to show improvement in outcome. We have previously reviewed this and concluded it was due, in large part, to poor performance of screening tests. Here, we report a study design where the primary aim is to generate clinically useful methods to screen women to assess their risk of adverse pregnancy outcome.

**Methods/design:**

We report the design of a prospective cohort study of unselected primiparous women recruited at the time of their first ultrasound scan. Participation involves serial phlebotomy and obstetric ultrasound at the dating ultrasound scan (typically 10–14 weeks), 20 weeks, 28 weeks and 36 weeks gestation. In addition, maternal demographic details are obtained; maternal and paternal height are measured and maternal weight is serially measured during the pregnancy; maternal, paternal and offspring DNA are collected; and, samples of placenta and membranes are collected at birth. Data will be analysed as a prospective cohort study, a case-cohort study, and a nested case-control study.

**Discussion:**

The study is expected to provide a resource for the identification of novel biomarkers for adverse pregnancy outcome and to evaluate the performance of biomarkers and serial ultrasonography in providing clinically useful prediction of risk.

## Background

The current pattern of provision of antenatal care for low risk women in the UK was established in 1929. Major changes have taken place in certain aspects of care, in particular, population-based screening for fetal abnormality [1]. These have been driven by technological developments in ultrasound, biochemical screening and molecular genetics. In contrast, the methods for screening the low risk population for other complications of pregnancy, in particular, intra-uterine growth restriction, pre-eclampsia and stillbirth, have remained largely unchanged over recent years [2]. The normal approach is to assess women for risk factors in their medical, gynaecological and obstetric history at the booking visit. This is followed by serial antenatal visits with a midwife which include measurement of the symphysis-fundal height with a tape measure, measurement of blood pressure with a sphygmomanometer, and urinalysis. The recent guideline from the UK National Institute for Clinical Excellence (NICE) on antenatal care addresses the assessment of "Fetal growth and well-being in unselected women" (section 1.10). The sole positive statement is that "Symphysis-fundal height should be measured and recorded at each antenatal appointment from 24 weeks" [3]. However, routine measurement of symphysis-fundal height had a sensitivity of less than 30% for detection of small for gestational age (SGA) infants, even though the relatively broad definition of birth weight less than the 10^th ^percentile for gestational age was employed [4].

One of the primary reasons for assessing fetal growth and well-being is to prevent stillbirth, defined as death of an infant in the perinatal period showing no signs of life. Stillbirth accounts for 60% of all perinatal deaths and 75% of all potentially preventable losses (defined as perinatal death of a normally formed infant weighing 1000 g or more) [5]. Analysis of the determinants of stillbirth leads to the conclusion that over half are related to placental dysfunction and that many of these are associated with impaired fetal growth [2]. Placental function can be assessed by utero-placental Doppler flow velocimetry and fetal growth can be assessed by ultrasonic fetal biometry. It would seem plausible that routine application of these tests may prevent stillbirth. However, meta-analysis of randomised controlled trials demonstrates that use of neither methodology reduced perinatal mortality when applied to unselected women [6,7]. Hence, in the UK and many other countries, it is not recommended that these tests are routinely offered to pregnant women. We have previously reviewed the literature around stillbirth and concluded "future work on population-based screening for stillbirth should be preceded by high-quality, non-interventional prospective cohort studies characterising the screening properties of new methods of risk assessment in an unselected population" [2]. Here we describe a protocol for such a study focusing on assessing and developing biochemical and ultrasonic indicators of placentation.

## Methods/design

The study design is a prospective cohort study. The cohort is defined as primiparous women with a singleton pregnancy who are attending for their dating scan at the hospital's ultrasound department. The initial conduct of this study is confined to a single centre (The Rosie Hospital, Cambridge, UK). However, it has the potential to be conducted at other centres.

### Recruitment and first appointment

Woman with a positive pregnancy test are told by their midwife to contact the ultrasound department to arrange a dating scan. When women contact the department, they are asked if they have had any previous pregnancies progress beyond 23 weeks. If they have not, a letter of invitation and a patient information leaflet for the study are sent. Women are approached following their dating scan. Hence those with non-viable or multiple pregnancies are not approached for consent. Consent is obtained by a research midwife. Participation is explained, any questions are answered and women who agree sign the consent form. The original is retained by the study, a copy is given to the participant and a copy is placed in her clinical case record. Routine antenatal care at the hospital involves an ultrasound scan at 20 weeks for a detailed anatomical scan of the fetus. For women who consent to the project, this appointment is made on a research list where the appointment is of one hour in duration (routine duration is 30 minutes). Appointments (30 minute) for research scans at 28 and 36 weeks are also made at this time and, finally, the participant is sent for phlebotomy.

### Second appointment

At the second appointment, each participant has their detailed scan of fetal anatomy. Any abnormalities or complications are dealt with by standard hospital protocols. At the time of the scan, further information is obtained, including maximum thickness of the placenta, the presence and dimensions of lakes, and umbilical and uterine artery Doppler flow velocimetry. The results of the research component of the scan are not reported. At this visit, a brief computer assisted questionnaire is conducted. The elements of this are tabulated (Table 1). Data from the first scan are also retrieved and all information is stored directly onto a custom built database linked to a web-based interface and designed using Microsoft SQL and ASP website. Maternal height and weight are also measured and phlebotomy performed. Pre-pregnancy weight is self reported.

**Table 1 T1:** Maternal demographic data

**Characteristics**
Name
Date of birth (dd/mm/yy)
Current age (yr)
Marital status (married/cohabitating/single)
Occupation (free text)
Partner's occupation (free text).
Discontinued full time education (Y/N)
Age full time education stopped (yr)
Smoking status
(never/quit pre-pregnancy/quit during pregnancy/currently smoking)
If currently smoking, number per day
Alcohol use (units per week)
Current
Pre-pregnancy
Current medical condition (free text)
Current prescription medication (free text)
Previous pregnancies ending less than 24-weeks (Y/N)
If yes 1. Gestational age (wks) 2. Spontaneous (Y/N)
Use of oral contraceptive pill in the last 3 months (Y/N)
Date of last menstrual period (dd/mm/yy)
Certain of date last menstrual period (Y/N)
Duration of menstrual cycle (/28 days)

The study also involves collection of a sample for DNA from the partner and this is usually obtained at the second appointment as the partner is often present for this scan. An information leaflet was offered for the woman's partner at the first visit. Where the partner attends, the research sonographer explains participation, answers any questions and obtains written consent to obtain a sample of saliva using the Oragene^© ^DNA collection kit. The partner's height and weight are also measured.

### Third and fourth appointment

These visits are conducted at 28 and 36 weeks gestational age, respectively. The formats for both are identical. A scan is performed which includes fetal biometry, amniotic fluid index, uterine and umbilical uterine artery Doppler flow velocimetry, and assessment of placental maturity. In addition, maternal weight is measured and phlebotomy is performed. Most of the scan information is concealed. The software on the machines which generates gestational age estimates based on biometry is disabled preventing ad hoc estimation of the appropriateness of measurements. Four items of information are revealed if present, namely (1) previously unrecognised major congenital abnormality, (2) previously unrecognised placenta praevia, (3) profound oligohydramnios (amniotic fluid index less than 5) and (4) presentation at 36 weeks.

### Phlebotomy and serum/plasma storage

Samples are taken into a plain tube and an EDTA tube for serum and plasma, respectively. They are spun in a centrifuge at 4°C, each sample is then separated into four aliquots and placed in a -40°C freezer. Twice a day samples are removed from the freezer and stored at -80°C. All are split into pairs and stored in separate freezers. All freezers are equipped with identical racking systems. The samples are placed in 1.8 ml tubes, with 81 tubes in a box. A total of 28 boxes are placed in a rack and the freezer contains 18 racks. Hence, each freezer has the capacity to store 40,824 tubes. The location and identity of all samples is stored using a sample inventory software package, Pro-Curo (Brady Laboratories), and samples are identified using a bar coded label. Samples for maternal DNA are stored as whole blood. The paternal salivary sample is processed and paternal DNA is also stored at -80°C. All freezers are connected to a secure power supply, supported by the hospital's emergency generator, which is regularly tested. All freezers are also equipped with a liquid CO_2 _back-up system (New Brunswick Scientific) which will maintain samples at less than -55°C for 20 hours in the event of failure of a freezer. All freezers are connected to a phone line and will send an automated message to technical staff in the event of a failure or a rise of temperature greater than -65°C. A third empty freezer is maintained at -80°C in order to accommodate samples in the event of failure of one of the main freezers.

### Delivery

Pregnant women receiving antenatal care in the UK National Health Service generally carry hand held notes. Women participating in the study have their hand held notes contained in a plastic folder with the study logo to flag their participation. Moreover, a sticker is placed in the delivery unit section of the notes to flag the need for placental collection and a sheet with instructions is included in the notes. This sheet includes the number for a phone held by the on-call technician. If a woman delivers at a time when a technician is present in the hospital, the placenta is passed to the technician as soon after delivery as practicable. The placenta is sampled as described in the schematic shown in Figure 1. Details of the collection protocol for the samples to be used for histological, DNA, RNA and protein analyses are given in Table 2. If the woman delivers at a time when there is no technician present, the placenta is placed in a dedicated fridge and the samples processed the following morning. The details again are described in Table 2.

**Figure 1 F1:**
[figure not shown]
Schematic of placental collection at delivery.

**Table 2 T2:** Placental Collection

**Immediate level Collection**	
Completed within 10 minutes of delivery of the placenta	
1. Placenta	Sites at the periphery of four lobules, free of visible infarction, calcification, haematoma or damage are identified. 1–2 mm of tissue is removed from the maternal surface (basal plate) and discarded. A "grape size" sample of placental tissue is then obtained from each site and washed repeatedly in chilled phosphate buffered saline. The following samples are obtained from each 'grape':
	i. RNA: Four 5 mg pieces placed in RNA later, (Applied Biosystems, Warrington, UK), and stored at -80°C.
	ii. DNA & protein: Four 50 mg pieces, frozen in liquid nitrogen and stored at -80°C.
	iii. Histology: A "pea-sized" sample is fixed in 3 ml of formalin (24 hours at 4°C) and embedded in paraffin wax.
2. Placental membranes	A 2 × 2 cm portion of the membranes is obtained and fixed in formalin as above.
3. Cord blood	A 10 ml anti-coagulated (EDTA/citrate) sample is obtained. Peripheral blood mononuclear cells are isolated and stored in liquid nitrogen.
4. Umbilical Cord	The following samples are obtained
	i. DNA & protein: Two 100 mg pieces of cord, frozen at -80°C.
	ii. Histology: One 5 mm transverse section of cord is fixed in formalin as above.

**Basic level collection**	
Placenta is stored in a fridge and sampled within 24 hours of delivery.	

1. Placenta	Four 'grape size' samples are obtained and washed as described above. From each 'grape' sample, the following are obtained:
	i. DNA & protein: Four 50 mg pieces, frozen at -80°C.
	ii. Histology: A "pea-sized" sample is fixed in 3 ml of formalin as above.
2. Placental membranes	A 2 × 2 cm portion of the membranes is obtained and fixed in formalin as above.
3. Umbilical cord	The following samples are obtained
	i. DNA & protein: Two 100 mg pieces of cord, frozen at -80°C.
	ii. Histology: One 5 mm transverse section of cord is fixed in formalin as above.

### Ethics

The study was approved by the Cambridge Local Research Ethics Committee 2. Ethics applications in the UK include a section, "A68. What are the main ethical issues with the research?" The issue flagged in this section was our decision to conceal most of the information retrieved in the research scans, with the exceptions listed above. The committee raised no concern regarding this arrangement but did request changes in the nature and presentation of the information in the patient information leaflets.

### Ascertainment of outcome

All outcomes will be ascertained by trained midwives performing direct examination of the woman's clinical record. Standardised definitions will be employed, such as the ACOG classification of pre-eclampsia [8]. In addition, the research database will be linked using the case record number to the hospital's IT systems. This will allow retrieval of routine blood investigations, other targeted ultrasonic investigations, and the Delivery Unit record. Details will also be obtained regarding admission of the infant to the neonatal intensive care or special care units.

### Analytic approach

The study design allows three major analytic approaches, namely, analysis as a cohort study, a case-cohort study or a nested case-control study. All three approaches are planned. Analysis as a cohort study will employ the information retrieved on all participants. This includes all the maternal demographic information, information on the partner, the mother's height and weight serially measured through the pregnancy, and the result of the research ultrasound scans. Analysis as a case-cohort design will be used to determine the associations and predictive ability of biochemical and genetic measurements on the stored samples. In this approach, a random sample of the cohort (the sub-cohort) is selected as the control group at the start of the study. Biochemical and genetic measurements are made on the sub-cohort and on all cases. The analysis for a given adverse event compares cases with the members of the sub-cohort who did not experience the given outcome. The advantages of the case-cohort study design are that a common group of controls can be selected for all adverse outcomes [9]. It has the advantage over simply performing the given biochemical assay on all cohort members of substantially reducing the costs of analysis with minimal loss of precision.

Case-cohort studies with time-to-event outcomes require non-standard statistical analyses but those with binary outcomes do not [10]. Thus statistical analysis of both cohort and case-cohort designs will be performed using logistic regression [11]. In order to avoid over-fitting of models, multivariate analyses will use a cross validation approach. A model will be fitted on 90% of the given study group and then the probability of the outcome calculated for each member of the remaining 10%. This process will be repeated until "out of sample" estimated probabilities are obtained for all participants in the given analysis. The screening performance of the models will be assessed using this predicted probability in two ways. First, the area under the receiver operating characteristic (ROC) curve will be estimated, with 95% confidence intervals as a summary of its discrimination. Different models will be compared using the method of DeLong et al [12]. Second, the screening performance of models will be assessed by analysis using percentiles of predicted probability, where women in the top 5%, 10% or 20% of predicted probability are regarded as screen positive. The screening performance of each of the thresholds will then be summarized in terms of sensitivity, specificity, positive and negative predictive values and likelihood ratios.

Finally, we also plan to conduct nested case-control studies within the cohort. This approach will be used where very expensive or labour intensive methodologies are planned, such as proteomic analysis of serum or gene expression array analysis of placental RNA, and will involve sampling of cases as well as controls. These methods are generally utilized in studies trying to understand the biology of adverse pregnancy outcome or to identify novel biomarkers. Nevertheless, the possibility of confounding is still present with these approaches. Multivariate analysis is impractical using these methods, given that small numbers are employed. Our approach is to perform a nested case-control design with one to one matching of cases and controls on key maternal characteristics to address the potential for confounding. Subsequent analyses will, therefore, utilise paired statistical methods.

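### For biomarkers analysed case-cohort, taking the top 5/10/20% cut-offs and PPV/NPV from the analysed set misstates the screen-positive rate, understates sensitivity at that rate and overstates PPV

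*Protocol article*

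**What the plan says.** All of this is in the protocol article under Analytic approach.

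- The association and predictive ability of biochemical and genetic measurements are to be assessed in a case-cohort design, whose controls are fixed in advance: "a random sample of the cohort (the sub-cohort) is selected as the control group at the start of the study".
- Assays are run for every woman in that sub-cohort and for every case arising anywhere in the cohort. The contrast is then set out as follows: "The analysis for a given adverse event compares cases with the members of the sub-cohort who did not experience the given outcome". Cases therefore enter at 100% and non-cases at the sub-cohort fraction, which is not given.
- On method: "Case-cohort studies with time-to-event outcomes require non-standard statistical analyses but those with binary outcomes do not". The next sentence draws the consequence: "Thus statistical analysis of both cohort and case-cohort designs will be performed using logistic regression".
- Cross-validation then runs until out-of-sample "estimated probabilities are obtained for all participants in the given analysis".
- Screening performance is judged by AUC, and also by percentile thresholds: "women in the top 5%, 10% or 20% of predicted probability are regarded as screen positive". Each threshold is "summarized in terms of sensitivity, specificity, positive and negative predictive values and likelihood ratios".

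The section on power calculations names sensitivity at a given screen-positive rate as a key measure.

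**The concern.** Sampling on the outcome changes only the intercept of a logistic model. Odds ratios, the ranking of women and the AUC survive it. A percentile of predicted probability does not, because it depends on how many cases are in the set over which it is taken. PPV and NPV depend on the same case mix.

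In a set enriched with cases, the top 5% is filled disproportionately by cases. The cut-off is too high, and fewer than 5% of screened women would exceed it. Three errors follow:

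- sensitivity at the nominal rate is understated;
- specificity at the nominal rate is overstated;
- PPV is overstated, because it reflects the case mix of the sample and not of the antenatal population.

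This touches the measure the article calls key. Ultrasound and demographic models are fitted on the full cohort and are not affected, so their results could not be compared with those of the blood and genetic markers at the same nominal rate.

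**Working it through.** **Inputs from the article.** Target cohort 4000; 3% incidence giving 120 cases; 0.5% incidence (stillbirth) giving about 20 cases; cut-offs at 5%, 10% and 20%.

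**Assumptions.** Sub-cohort fraction f from 5% to 50%; a binormal marker with equal variances and AUC 0.80. The article gives neither.

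**The article's own figures.** 0.03 × 4000 = 120. Exact (Clopper-Pearson) intervals at 80% sensitivity are 73.8–85.3% (200 cases), 70.8–87.3% (100), 66.3–90.0% (50) and 56.3–94.3% (20), which match the stated intervals. They describe precision only, so they would not reveal a misplaced cut-off.

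**Step 1: case mix.** With D cases among N women, prevalence in the analysed set is p = D / [D + f(N − D)]. At f = 10%: 120 / (120 + 388) = 120/508 = 23.6%, against 3% in the cohort.

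**Step 2: ceiling on sensitivity.** The top q of the set cannot hold more than a share q/p of the cases. At q = 5% this is 0.05/0.236 = 21%; at q = 10% it is 42%. A perfect marker could not exceed these values.

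**Step 3: cut-off.** For AUC 0.80 the separation is d = √2 × z(0.80) = 1.19. Solve p·[1 − Φ(t − d)] + (1 − p)·[1 − Φ(t)] = q for t. Then sensitivity = 1 − Φ(t − d), specificity = Φ(t), PPV = p × sensitivity / q and NPV = (1 − p) × specificity / (1 − q). The full-cohort values use p = 0.03.

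3% incidence, 4000 women, AUC 0.80:

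| Cut-off | f | Sensitivity | PPV | NPV |
|---|---|---|---|---|
| top 5% | full cohort | 30% | 18% | 98% |
| top 5% | 50% | 27% | 32% | 96% |
| top 5% | 20% | 22% | 58% | 89% |
| top 5% | 10% | 16% | 77% | 79% |
| top 5% | 5% | 12% | 89% | 64% |
| top 10% | full cohort | 44% | 13% | 98% |
| top 10% | 50% | 42% | 24% | 96% |
| top 10% | 10% | 29% | 69% | 81% |

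**Step 4: what the nominal 5% means.** At f = 10% the cut-off is t = 2.17, with sensitivity 16.3% and specificity 98.5%. Among screened women the positive rate is 0.03 × 0.163 + 0.97 × 0.015 = 1.9%. The true PPV at that same cut-off is 0.03 × 0.163 / 0.0194 = 25%. The reported 77% therefore matches neither the PPV at the cut-off used (25%) nor the PPV at a true 5% rate (18%).

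**Step 5: rare outcome.** At 0.5% incidence and f = 10%, p = 20/(20 + 398) = 4.8%. At the top 10%, sensitivity is 42% against 46%, but PPV is 20% against 2.3%.

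**Step 6: does weighting repair it?** A simulation (100 replicates, 10-fold cross-validated logistic regression, 3% incidence, f = 10%, AUC 0.75) weighted non-cases by 1/f in setting the percentile and computing PPV. At 5/10/20% it gave sensitivity 23/36/54% and PPV 14/11/8%. The full-cohort values are 22.8/35.4/53.0% and 13.7/10.6/7.9%.

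**The case against.** The best defence is that the article never says the percentiles are unweighted. Its statement on binary outcomes leads to a choice of model, and as such it is correct. A screen-positive rate naturally means a rate among screened women. The sub-cohort is a random sample of the cohort, so percentiles taken within it would be right by design. A condensed article may leave the reference distribution to a fuller document.

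Part of this stands: the unweighted reading is an inference. It is nevertheless the natural one. The article does more than stay silent: it says that no special analysis is needed, forms probabilities for everyone in the given analysis, and applies one set of thresholds and predictive values to both designs.

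The size is also open to challenge. A 10% sub-cohort is only an example, and the article claims minimal loss of precision. For a simple case/non-case comparison, f = 10% raises the variance by about 27% (1/120 + 1/388 against 1/120 + 1/3880), while f = 50% raises it by about 3%. At f = 50% the sensitivity error is two to three points. This stands, although the article also expects substantial cost savings, which argues for a fraction well below 100%. The PPV error persists even at f = 50%: 32% against 18%.

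A reader might infer that every biomarker's screening performance will be wrong. The documents do not support that. AUC and DeLong comparisons, the first of the two planned assessments, are unaffected. Sensitivity, specificity and likelihood ratios are valid for the marker cut-off actually used; only its percentile label is wrong. The matched case-control studies, such as proteomics, use paired methods and lie outside this procedure.

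**Conclusion.** The concern holds within limits. As written, the procedure gives wrong percentile cut-offs, wrong sensitivity and specificity at the nominal screen-positive rate, and wrong PPV and NPV for biomarkers analysed case-cohort. The direction is fixed for any informative marker and any f below 100%: sensitivity too low, PPV too high, NPV too low.

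The size depends on f, the incidence and the marker. At 3% incidence and AUC 0.80, over f from 5% to 50%, top-5% sensitivity runs from 12% to 27% against 30%, and PPV from 89% to 32% against 18%. For a rare outcome the sensitivity error is a few points at f = 10%, while PPV is roughly nine-fold too high (20% against 2.3%). These figures rest on the assumed fraction, AUC and binormal marker, and on reading the percentiles as those of the analysed set.

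No recruitment, sampling or assay decision depends on this. It should still be corrected before any case-cohort screening result is reported, because sensitivity at a given screen-positive rate is a measure the article calls key.

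**What to change.** - Limit the statement that binary case-cohort outcomes need no special analysis to odds ratios and AUC (including DeLong comparisons). It need not be deleted.
- State that in case-cohort analyses the 5%, 10% and 20% cut-offs come from the cohort distribution of predicted probability. Either weight cases 1 and sub-cohort non-cases 1/f, or take the percentiles from the whole random sub-cohort, including those of its members who became cases.
- Compute PPV and NPV with the same weights, or by Bayes' rule from full-cohort incidence and the sensitivity and specificity at the corrected cut-off. Bayes' rule alone, at an uncorrected cut-off, leaves the rate mislabelled (in the example above, 25% PPV at a true rate of 1.9%).
- State f, and let the confidence intervals reflect the sampling of cases and sub-cohort, for example by resampling the two separately.
- Use a log-sampling-fraction intercept offset only if absolute risks from an unweighted fit are reported. It shifts every logit by the same amount, so it cannot move a percentile cut-off, and added to a weighted fit it would correct twice.

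The cost is a few sentences of plan text and a few lines of code. The sampling fraction and the cohort incidence will be known, and no new data are needed.

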The initial target recruitment for the present study is 4000 women. We estimate that this would yield approximately 120 cases of small for gestational age infants (using the strict definition of <3^rd ^percentile), 150–200 preterm births, and about 80 cases of significant pre-eclampsia (the number of cases of pre-eclampsia will depend on the stringency of the diagnosis). These should be adequate for most analyses planned. However, antepartum stillbirth unrelated to congenital abnormality affects about 0.5% of unselected primigravid women who attend for prenatal screening [15]. Hence, we would anticipate only approximately 20 such events. This is the basis for planning open-ended recruitment. However, samples from small numbers of women experiencing rare events will still be used to identify novel biomarkers using techniques such as proteomics and there may be potential to validate candidate markers in other cohorts. We will also use non-lethal complications of pregnancy, such as intra-uterine growth restriction, abruption and severe pre-eclampsia, as proxies for stillbirth. This is consistent with the view that similar processes operate in the lethal and non-lethal manifestations of these conditions [24].

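### One tenfold cross-validation pass with pooled probabilities makes results at about 20 cases depend on the random split; outcome-stratified, repeated partitions would largely remove this

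*Protocol article*

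**What the plan says.** The Analytic approach section of the protocol article says that "multivariate analyses will use a cross validation approach" to guard against over-fitting. The procedure is then given: "A model will be fitted on 90% of the given study group and then the probability of the outcome calculated for each member". The members meant are the women in the tenth left out of the fit. The repetition has a stopping point, which is when out-of-sample "estimated probabilities are obtained for all participants in the given analysis". Each woman therefore ends with one probability from one partition.

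Both performance summaries use that pooled quantity: "The screening performance of the models will be assessed using this predicted probability in two ways". The first is the area under the ROC curve with a 95% confidence interval, with models compared by the DeLong method. The second is a ranking in which "women in the top 5%, 10% or 20% of predicted probability are regarded as screen positive".

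The section does not say how the tenths are drawn, whether they are balanced on outcome, or whether a second partition is ever used.

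On case numbers, the Discussion states: "The initial target recruitment for the present study is 4000 women". It expects about 120 infants below the 3rd percentile, 150 to 200 preterm births and about 80 cases of significant pre-eclampsia. For antepartum stillbirth it says "we would anticipate only approximately 20 such events".

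**The concern.** Pooling the predictions of ten separately fitted models into one ranking assumes that the ten sets of probabilities share a scale. With few cases they may not. If the tenths are drawn without regard to outcome, a tenth that happens to hold many cases leaves fewer cases for fitting. The fitted baseline risk is then lower, and so are the probabilities given to that tenth. Its cases are ranked too low against women in other tenths, which pulls the pooled AUC down.

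Separately, and however the tenths are drawn, a single pass ties the reported figures to one random allocation. Another allocation of the same women would give another AUC and another sensitivity.

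The AUC and the sensitivity at a fixed screen-positive rate are the quantities the study sets out to report, and stillbirth is the outcome that motivates it. At stake is some avoidable noise, and possibly some avoidable pessimism, in the results for outcomes with very few cases.

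**Working it through.** **Inputs from the protocol article**

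- Fit on 90%, predict 10%, one probability per woman, pooled (Analytic approach).
- Target 4000 women. Expected cases: about 20 stillbirths (0.5% × 4000 = 20), about 80 pre-eclampsia, 120 below the 3rd percentile (3% × 4000 = 120) (Power calculations and Discussion).
- 95% intervals for a sensitivity of 80%: 74–85% (200 cases), 71–87% (100), 66–90% (50), 56–94% (20) (Power calculations).

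**Assumptions, because the article gives no figures.** 5 or 10 independent normal predictors, one of them informative, with cases shifted by 0.75 or 1.2 SD. The number of non-cases is 380 to 1980, because the case-cohort analyses use a sub-cohort of unstated size.

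**Step 1: the plan's own figure.** Exact (Clopper–Pearson) binomial intervals for 80% are 73.8–85.3, 70.8–87.3, 66.3–90.0 and 56.3–94.3%. All four stated intervals are reproduced. They describe sampling error only and contain no split-to-split variation.

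**Step 2: how uneven unstratified tenths would be.** For N women, c cases and tenths of size m = N/10, the chance that at least one tenth holds no case is

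Σ_j (−1)^(j+1) · C(10, j) · C(N − jm, c) / C(N, c).

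- N = 4000, c = 20: 78%
- N = 400, c = 20: 76%
- N = 2000, c = 80: 0.2%

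An empty tenth does not by itself invalidate a pooled AUC. It shows how unequal the training sets can be.

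**Step 3: simulated tenfold logistic cross-validation.** Unstratified and outcome-stratified tenths were compared on the same data sets. Differences are paired; the true AUC is that of the models fitted on 90%.

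| Cases / non-cases | Predictors, shift | AUC, unstratified minus stratified (SE) | Unstratified minus true | Stratified minus true | Split SD of AUC, unstratified | Split SD of sensitivity at top 10%, unstratified |
|---|---|---|---|---|---|---|
| 20 / 380 | 5, 0.75 | −0.021 (0.001) | −0.038 | −0.018 | 0.021 | 3.9 points |
| 20 / 380 | 5, 1.2 | −0.012 (0.001) | −0.026 | −0.014 | 0.013 | 3.7 points |
| 20 / 380 | 10, 0.75 | −0.018 (0.001) | −0.026 | −0.008 | 0.022 | 4.1 points |
| 80 / 1120 | 5, 0.75 | −0.006 (<0.001) | −0.010 | −0.003 | 0.005 | 1.4 points |
| 120 / 1080 | 5, 0.75 | −0.003 (<0.001) | −0.002 | +0.001 | 0.004 | 1.0 point |

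The SEs of the two columns against the true AUC are about 0.004 to 0.007, so only the paired column is precise.

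With 20 cases and 1980 non-cases (10 predictors, shift 0.75) the pooled AUC is 0.617 unstratified and 0.633 stratified, a difference of 0.016. The split SD falls from 0.019 to 0.014. Over the 20-case settings with an informative predictor, stratified tenths still leave a split SD of about 0.008 to 0.016 for the AUC, so stratifying alone does not settle the single-pass problem.

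A separate simulation with 4000 women, 20 cases and 5 predictors (3 informative) agrees. The fitted model's true AUC is 0.669. One unstratified pass gives 0.635 on average, and stratified tenths repeated five times give 0.655. The gain is 0.655 − 0.635 = 0.020 and the remaining shortfall is 0.669 − 0.655 = 0.014.

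**Step 4: size against sampling error.** For a sensitivity of 80% with 20 cases, the binomial SE is √(0.8 × 0.2 / 20) = 0.089. Adding a split SD of 0.04 gives √(0.089² + 0.04²) = 0.098, and 0.098 / 0.089 ≈ 1.10, about 10% wider.

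**The case against.** Four things can fairly be said for the plan.

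- **Stratification is not addressed.** A reader might infer that the tenths are drawn blind to outcome. The article does not say so, and an article commonly leaves fold allocation to the full protocol or analysis plan. This stands. The loss in AUC from unbalanced tenths is therefore conditional. The single pass and the pooling are different: they follow from the procedure as written.
- **The main outcomes are hardly touched.** A reader might infer that every outcome is affected. With the 80 to 120 or more cases expected for pre-eclampsia, small infants and preterm birth, the AUC effect is 0.003 to 0.006 or less. This stands.
- **Stillbirth is already treated as under-powered.** The Discussion plans open-ended recruitment, biomarker discovery with possible validation in other cohorts, and non-lethal complications as proxies. The article does not commit to a multivariable model on 20 stillbirths. This stands in part: the cross-validation is described for multivariable analyses in general, and no counts are given for some of the proxies, such as abruption and severe pre-eclampsia.
- **Sampling error dominates, and the bias is conservative.** The article already shows 56–94% for 20 cases, and a low AUC does not flatter a single model. Both are true. But split noise, unlike sampling error, can be nearly removed without new data, and undue pessimism could cause a useful marker for a rare outcome to be dropped.

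**Conclusion.** The point holds, as a modest one. The article describes a single tenfold pass with pooled probabilities and does not state that the tenths are balanced on outcome. At about 20 cases, one pass makes the result depend on the split, with an SD of about 0.01 to 0.02 for the AUC and 3 to 4 points for sensitivity at the top 10%. If the tenths are not stratified, the pooled AUC is a further 0.01 to 0.02 lower than it would be with stratified tenths. At 80 to 120 cases these effects are small, and at 20 cases the split widens the error of sensitivity by only about 10%.

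The sizes rest on the assumed number of predictors, effect sizes and numbers of non-cases. Two sets of assumptions gave similar answers at 20 cases. It would go too far to say that the planned AUCs are biased in general or that the method is invalid: tenfold cross-validation with pooled predictions is a standard method, and the documents support a concern only where cases are very few.

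**What to change.** State in the analysis plan that:

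1. the tenths are drawn separately within cases and within non-cases;
2. the whole tenfold process is repeated over many random partitions with stored seeds;
3. each woman's out-of-sample probability is averaged over the repeats, and that single averaged probability is used for the ROC curve, its confidence interval, the DeLong comparisons and the top 5%, 10% and 20% thresholds;
4. the between-partition spread is reported for low-count outcomes.

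Averaging the probabilities is preferable to averaging the AUCs. It keeps one score per woman, so the planned intervals and DeLong comparisons remain defined. In simulation at 20 cases the two gave practically the same AUC.

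The cost is a few sentences and computing time; no new data are needed. The change does not remove all the downward bias: with stratified tenths at about 20 cases, a shortfall of about 0.01 to 0.02 in AUC remained.
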